**Methods/design:**

This is a randomized controlled clinical trial to be conducted in the Medani Maternity Hospital, Sudan. Women aged 18–40 years that are diagnosed with preterm labor and have a gestational age between 25 and 34 weeks will be eligible to participate in this trial. The diagnosis of threatened PTL is defined as persistent uterine contractions “(four contractions every 20 min or eight contractions every 60 min)” with cervical changes “(cervical effacement ≤80% or cervical dilatation >two cm)”. Patients will be eligible regardless of the presentation of the fetus. It will be randomly decided whether participants receive nifedipine/indomethacin combination therapy or nifedipine monotherapy. The primary outcome is the number of women who do not deliver and do not need alternative tocolytic drug (terbutaline). The secondary outcome is an estimated association with neonatal morbidity and mortality. The sample size will be 117 subjects in each arm of the study, according to a type I error of 0.05 and a study power of 80%.

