### Sample size

Each study group will consist of 117 women, a number calculated based on a previous study [17]. We expect the proportion of successful outcomes (the number of women who do not deliver and who do not need alternative treatment for 48 h) in nifedipine monotherapy to be 72.0%, and we expect it to be 89.0% in the combination group. This sample size (117 in each arm) was necessary to achieve a 95% confidence level with a 5% margin of error and 80% power.

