### Analysis

Statistical analysis will be performed by using the SPSS version 22.0 (IBM) program (intention-to-treat analysis). In the evaluation of the study data, descriptive statistical methods (mean, standard deviation, minimum, maximum, median, frequency, and ratio) will be used. Student’s *t*-test will be used to compare quantitative data for normally distributed data, and if the distribution is not consistent with a normal distribution, the Mann–Whitney *U* test will be used to compare the variables between women in each arm of the study. Pearson’s chi-squared and Fisher’s exact tests will be used for qualitative data comparisons. Number needed to treat (NNT) for benefits and number needed to harm (NNH) for adverse outcomes with their 95% confidence outcomes will be calculated. A *p*-value> 0.05 will be considered statistically significant.

The groups (nifedipine/indomethacin combination group or nifedipine monotherapy group) will be analyzed as group A and group B, and confidentiality will be preserved. The identification of groups will be revealed only after the analysis is finished with the tables ready.

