## Discussion

We are expecting a higher effectiveness of the combination indomethacin/nifedipine tocolytic therapy compared with nifedipine monotherapy. Among the various tocolytics, nifedipine seems to be the most appropriate therapy for PTL [15]. However, it has been suggested that combination therapy is a good option for postponing of PTL [16]. Our findings will be supported by the recent findings of Kashanian et al. who enrolled 150 participants; these investigators reported that 89.4% of the combination-therapy patients compared to 72.0% of the patients in either a nifedipine or indomethacin monotherapy group had inhibition of uterine contractions for 48 h. Accordingly, the investigators indicated combination therapy be employed for inhibiting preterm labor, delaying delivery, and prolonging the duration of pregnancy [17].

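### The significance rule is printed with its inequality reversed, very probably by a sign slip, and it contradicts the plan's own 5% type I error

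*Protocol article*

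**What the plan says.** The Analysis section names the t-test, the Mann–Whitney test and, for categorical outcomes, says "Pearson’s chi-squared and Fisher’s exact tests will be used for qualitative data comparisons". It adds numbers needed to treat and to harm with 95% intervals. It then gives one threshold for all of these: a p-"value> 0.05 will be considered statistically significant". The document states no other significance rule.

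The error rates appear in two other places. The Abstract (Methods/design) sets the group size "according to a type I error of 0.05 and a study power of 80"%. The Sample size section says: "This sample size (117 in each arm) was necessary to achieve a 95% confidence level with a 5% margin of error and 80% power". That section expects success "in nifedipine monotherapy to be 72.0%, and we expect it to be 89.0% in the combination group". The Discussion gives the direction hoped for: "We are expecting a higher effectiveness of the combination indomethacin/nifedipine tocolytic therapy compared with nifedipine monotherapy".

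**The concern.** A p-value measures how surprising the data would be if the arms did not differ, so evidence of a difference lies at small values. The printed rule assigns significance to large ones. Apart from a p-value of exactly 0.05, it would reverse the conclusion of every comparison it touches.

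The sentence is not tied to one endpoint. It governs the 48-hour effectiveness outcome, the maternal adverse effects that the Outcome measurements section also lists under primary outcomes, and the secondary pregnancy and neonatal outcomes. A published protocol is the reference against which the final report will be checked. As printed, a correct analysis departs from the protocol, and one that complies with it reaches the wrong conclusions. The trial is open-label and its authors expect the combination to do better, so the decision rule should be unambiguous in advance.

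**Working it through.** **Inputs.** Success rates 72.0% and 89.0%, 117 per arm, 80% power (Sample size). Type I error 0.05 (Abstract). Pearson chi-squared for binary outcomes (Analysis). Sidedness is not stated; two-sided is assumed and one-sided is shown as the alternative. Expected cell counts are comfortably large for Pearson's test: the smallest is 117 × 0.195 ≈ 22.8 under the pooled failure rate.

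**1. The plan's own figure.** With pooled rate (0.72 + 0.89)/2 = 0.805:

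n = [1.96 × √(2 × 0.805 × 0.195) + 0.8416 × √(0.72 × 0.28 + 0.89 × 0.11)]² / 0.17²

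= (1.098 + 0.461)² / 0.0289 ≈ 84.1, so 85 per arm.

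With continuity correction it is 96. One-sided it is 67, or 78 with correction. The stated 117 is not reproduced from the stated inputs; it is larger than they require. This is a separate matter that neither supports nor weakens the present point. The calculations below simply take 117 per arm as given.

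**2. Power at 117 per arm under the usual rule, p < 0.05 (normal approximation).**

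- Standard error with no difference: √(2 × 0.805 × 0.195 / 117) = 0.0518
- Standard error at the planned rates: √[(0.2016 + 0.0979) / 117] = 0.0506
- z = (0.17 − 1.96 × 0.0518) / 0.0506 ≈ 1.35, giving power of about 0.912

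**3. Exact enumeration.** Sum the product of the two binomial probabilities (n = 117 each) over every pair of success counts whose two-sided Pearson p-value meets the rule.

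| True rates | P(p < 0.05) | P(p > 0.05), the printed rule |
|---|---|---|
| 72% vs 72% | 0.050 | 0.950 |
| 89% vs 89% | 0.051 | 0.949 |
| 72% vs 89% | 0.920 | 0.080 |

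With a continuity-corrected statistic, the printed-rule column becomes 0.964, 0.971 and 0.112. With a one-sided test, the normal-approximation power at the planned rates is 0.953, so the printed rule would declare significance with probability 1 − 0.953 = 0.047.

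**4. Comparison with the stated error rates.** The plan claims a 5% type I error and 80% power. The corrected rule gives about 5% and 92%, which meets both. The printed rule gives about 95% and 8%, which meets neither. None of the variants tried (continuity correction, one-sided test) brings the printed rule near the stated figures.

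**The case against.** The strongest reply is that the intent is obvious. The type I error of 0.05, the 95% confidence level, the 95% intervals for the numbers needed to treat and harm, and the expectation of a benefit all point to p < 0.05. The software reports p-values and does not apply the sentence. Randomisation, sample size, data collection, tests and estimates are untouched. A competent analyst would read the sign as a misprint and carry on.

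Most of this stands, and it limits how far the point goes. A reader might infer that the trial will run with a 95% false-positive rate, or that its authors chose to treat null results as positive. The documents support neither. The 95% and 8% figures describe the sentence taken literally and do not forecast what will be done.

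The reply does not make the sentence right. No other place in the document states the rule correctly, so a reader must infer it from the sample-size figures. Nor is there any sign that the symbol was corrupted when the text was read from the PDF: the same sign is used sensibly elsewhere, for example in the cervical dilatation and maternal temperature criteria under Patients. A misreading cannot be excluded without the PDF, but nothing points to one.

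**Conclusion.** Wrong as written. The document's only significance rule has its inequality reversed and contradicts the error rates in the Abstract and the Sample size section. The likely cause is a slip of one sign.

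Taken literally, with 117 per arm and a two-sided Pearson chi-squared test, the rule declares significance about 95% of the time under no difference and about 8% of the time at 72% versus 89%, against about 5% and 92% once corrected. These figures rest on the assumption of two-sided testing and on the plan's own success rates. The contradiction itself rests on neither.

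**What to change.** Change the sentence in the Analysis section to: *A p-value < 0.05 will be considered statistically significant.* Keep its present scope, so that it still covers every test now under it. Restricting it to the primary outcome would leave the safety and secondary comparisons with no stated threshold.

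As a separate clarification, state that the tests are two-sided. This is an addition and not part of the correction, since the document gives no sidedness; the authors should confirm that it is what they intend.

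The cost is one character, published as a short correction and carried into any analysis plan that repeats the sentence. Sample size, data collection and patient care do not change.

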## Discussion

We are expecting a higher effectiveness of the combination indomethacin/nifedipine tocolytic therapy compared with nifedipine monotherapy. Among the various tocolytics, nifedipine seems to be the most appropriate therapy for PTL [15]. However, it has been suggested that combination therapy is a good option for postponing of PTL [16]. Our findings will be supported by the recent findings of Kashanian et al. who enrolled 150 participants; these investigators reported that 89.4% of the combination-therapy patients compared to 72.0% of the patients in either a nifedipine or indomethacin monotherapy group had inhibition of uterine contractions for 48 h. Accordingly, the investigators indicated combination therapy be employed for inhibiting preterm labor, delaying delivery, and prolonging the duration of pregnancy [17].

### Limitations

It is desirable to have a blinded clinical trial in this situation; however, this might be difficult to conduct in our setting. There is an expected degree of bias due to the lack of blinding in this protocol and this might affect the results of the trial. Some inflammatory markers will not be assessed and this could be one of the limitations.

## Data Availability

All individual participant data and materials collected during the trial will be shared after deidentification. Will make the database available upon reasonable request. The data and material-sharing time frame will begin 3 months after trial completion and end 11 months following trial completion. During the mentioned time frame, data will be shared with anyone who wishes to access it for any type of analysis or purpose. The time planned for this study is 24 months, which is further divided into two major phases. The 1st phase is the preparation of the study tools and materials. The second phase is applying the trial methods mentioned above. The expected date of trial initiation is June 20th 2020. Further details of the study plan are mentioned in the table below (Tables 1 and 2):

## Abbreviations

PTL: Preterm labor
BMI: Body mass index
OR: Odd ratios
CI: Confidence interval
